### Outcome Measurements

#### Primary Outcome

The primary outcome will be the area under the curve (AUC) of overall pain in the first 24 hours after surgery, assessed on an NRS of 0 to 10 administered by a nurse blinded to study group allocation.

AUC for overall pain will be calculated on the NRS measurements at predetermined time points (30 min, 60 min, 120 min, 4 hours, 8 hours, 12 hours, and 24 hours) plus any time when rescue analgesic is requested.

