### Sample Size Calculation

A sample size determination was conducted for the main outcome variable. Hypothesizing an AUC for overall pain in the first 24 hours of 144 patients in group B and 120 patients in group A, a common SD of 60, 140 patients per group will be necessary to achieve 92% power with an alpha error of 5% with a 2-sided *t* test for independent samples.

On the basis of preliminary results of a pilot study conducted at the Catania center, we expect to lose no more than 5% of patients because of surgery durations >90 min; thus, we plan to enroll 300 patients to be allocated in the ratio 1:1 in 2 groups.

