### Statistical Analysis

#### Statistical Methods for Analyzing Primary and Secondary Outcomes

The primary endpoint (AUC for pain) will be compared by Student *t* test. *P* value <.05 will be considered significant. Descriptive statistics will be obtained for all variables assessed in the study population. Mean and SD will be used for normally distributed variables, and mean and interquartile range will be used for skewed distributions and proportions for categorical variables. Whenever relevant, 95% CIs will be calculated.

For group comparisons, Student *t* test (rank-sum test or Mann–Whitney test for skewed distributions) will be used for quantitative variables (analysis of variance or Kruskal-Wallis for >2 groups, respectively) and Pearson chi-square test (Fisher exact test where appropriate) for categorical variables. Two-tailed tests will be used in all cases. *P* value <.05 will be considered significant.

Generalized mixed models will be used to assess differences between groups in endpoints measured at several time points.

A detailed statistical analysis plan will be developed after the first 40 patients have been enrolled.

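### The primary 24-hour pain AUC is compared without a baseline pain score; using one as a covariate would be a cheap, minor gain in precision

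*Protocol article*

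**What the plan says.** Under Primary Outcome, the Protocol article states: "The primary outcome will be the area under the curve (AUC) of overall pain in the first 24 hours after surgery". The same section then sets out which scores enter it: "AUC for overall pain will be calculated on the NRS measurements at predetermined time points (30 min, 60 min, 120 min, 4 hours". The list goes on to 8, 12 and 24 hours and adds any score taken when a patient asks for rescue analgesia. All of these times are after surgery.

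Under Statistical Methods for Analyzing Primary and Secondary Outcomes, it states: "The primary endpoint (AUC for pain) will be compared by Student". The test meant is the unadjusted t test, and no covariate is named. The same section announces a detailed statistical analysis plan, to be written once 40 patients have been enrolled.

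Sample Size Calculation gives the planning values: "Hypothesizing an AUC for overall pain in the first 24 hours of 144 patients in group B and 120 patients in group A" (read here as mean AUCs, not patient counts), then "a common SD of 60", and finally "140 patients per group will be necessary to achieve 92% power with an alpha error of 5% with a 2-sided". The test named there is likewise the t test.

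Three other places bear on the point:
- **Eligibility:** surgery for endometriosis is excluded. No criterion excludes women who already have pain.
- **Contacts before allocation is known:** there is a presurgery visit (Ethical Issues), and premedication is given in reception before induction (Preparation for Surgery and Induction of Anesthesia). The envelope is opened only at induction (Allocation Concealment Mechanism).
- **Table 2:** the site-specific pain AUCs (intrascapular, incisional, lower abdomen) also use predefined time points.

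**The concern.** The outcome is overall pain. A woman's AUC therefore reflects any pain she had before surgery that persists, and her own way of using a 0 to 10 scale, as well as the effect of the operation. An unadjusted t test leaves all of that between-patient variation in the error term. A preoperative score is the natural covariate for removing part of it, and the article neither lists one nor uses one.

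At stake are the width of the confidence interval and the ability to see and adjust for a chance imbalance in prior pain. Timing matters. A covariate can be added to an analysis plan later, but a score that was not taken before surgery cannot be recovered. If none is being taken and the question first comes up when the analysis plan is written, the first 40 of 300 women (40/300 = 13%) would have no baseline value.

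**Working it through.** **Inputs from Sample Size Calculation.** Means 144 and 120, so the difference is 24 NRS x hours; SD 60; 140 per group; two-sided 5%.

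**Input not in the documents.** The correlation r between a preoperative NRS and the 24-hour AUC. It is assumed here over 0.1 to 0.5.

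**Step 1: the plan's own figure.**
- SE of the difference = 60 × √(2/140) = 7.17.
- Noncentrality = 24/7.17 = 3.35, with 278 degrees of freedom.
- Power = 91.5% by the noncentral t and 91.7% by the normal approximation. The stated 92% is reproduced.
- The normal approximation asks for 142 per group for 92% power, against 140 stated, which agrees closely.

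**Step 2: adjustment for a baseline score.** Residual SD = 60 × √(1 − r²), put into the same power formula. The equivalent gain in sample size is 1/(1 − r²).

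| r (assumed) | Residual SD | Power, 140 per group | n per group for 92% (normal) | Sample size factor |
|---|---|---|---|---|
| none | 60.0 | 91.5% | 142 | 1.00 |
| 0.1 | 59.7 | 91.8% | 141 | 1.01 |
| 0.2 | 58.8 | 92.6% | 136 | 1.04 |
| 0.3 | 57.2 | 93.8% | 129 | 1.10 |
| 0.4 | 55.0 | 95.3% | 119 | 1.19 |
| 0.5 | 52.0 | 97.1% | 107 | 1.33 |

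The variance falls by r², so by 1% to 25% over this range. The covariate takes one of 278 degrees of freedom, which is negligible.

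**Step 3: size of a chance imbalance.** The target difference equals one NRS point held for 24 hours (24/24 = 1). Assume a preoperative NRS SD of 1 to 2, which the documents do not give.
- SE of the difference in baseline means = SD × √(2/140) = 0.12 to 0.24 points.
- If carried in full for 24 hours, that is 2.9 to 5.7 AUC units.
- An imbalance of 1.96 SE would be about 5.6 to 11.2 units, or 23% to 47% of the target difference. Carrying it in full is the extreme case.

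This scatter is part of the outcome SD of 60, so the t test's standard error already covers it.

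**Step 4: why a covariate and not a change score.** Subtracting 24 × baseline from the AUC gives variance 60² + (24s)² − 2r × 60 × 24s, where s is the baseline SD. With s = 2 and r = 0.2 (both assumed), this is 3600 + 2304 − 1152 = 4752. The SD is then 68.9 and power falls to 82.7%. Subtraction can lose precision; regression on the baseline score avoids that.

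**The case against.** Four objections carry weight.

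**Silence is not absence.** A reader might infer that the trial collects no preoperative pain score. The article does not say so. The quoted list covers scores that enter an AUC starting after surgery, so a preoperative score would not appear there even if it were recorded. A condensed article may leave baseline items to the full protocol. This stands, and the fix is conditional for that reason. It does not touch the stated primary test, which is unadjusted.

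**No bias.** A reader might also infer that counting prior pain as postoperative pain distorts the treatment comparison. The documents do not support that. Allocation is randomised 1:1, so prior pain has the same expectation in both arms and cancels in the expected difference. The declared outcome is overall pain, with no claim to isolate new pain. Type I error and interval coverage are sound without a baseline. This stands in full.

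**The gain may be small.** Power is already about 92%. At r = 0.1 the gain is 0.3 points, and at 0.2 to 0.3 it is 1.1 to 2.3 points. Nothing in the documents supports 0.4 or 0.5, and excluding endometriosis surgery removes one potentially painful indication. If most women score near zero beforehand, the covariate carries little information. This also stands and limits the point to a minor one.

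**Not every site has a baseline.** Incisional pain cannot exist before the incision. A preoperative score has meaning only for the intrascapular and lower abdominal sites. This stands.

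What remains is that the stated test is less efficient than an equally simple alternative. The announced analysis plan can supply the model, but it cannot supply scores that were not taken.

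**Conclusion.** The point holds as a minor improvement in efficiency. The planned comparison is valid and reaches about the power claimed for it. As written, it does not use whatever precision a preoperative pain score could give. Over an assumed correlation of 0.1 to 0.5, the gain runs from 0.3 to 5.6 power points (91.5% to between 91.8% and 97.1%), equivalent to 1% to 33% more patients. The range rests on the plan's SD of 60 and on a correlation that the documents do not give; near zero, nothing is gained. Neither a biased comparison nor a proven failure to collect baseline pain can be concluded from the article.

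**What to change.** 1. State whether a preoperative overall-pain NRS is recorded. If not, add one, taken before premedication and before the envelope is opened, at a contact that already takes place. Settle this before enrolment starts and not when the analysis plan is written.
2. Replace the primary t test with a linear regression of the 24-hour AUC on arm, with the preoperative score as covariate. Report the adjusted difference with its 95% CI.
3. Impute a missing baseline score by the overall mean across both arms, so that no patient is dropped.
4. If the site-specific AUCs are to be adjusted as well, take baseline scores for intrascapular and lower abdominal pain only, and none for incisional pain.

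**Cost.** One spoken question, or three with the two sites, a few case report form fields, and one degree of freedom per model. No extra visits, staff or patients are needed, and the sample size can stay as planned. If the correlation is near zero, the effort brings no gain in precision.

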#### Secondary Outcomes

Secondary outcomes are summarized in Table 2.

Procedures lasting >90 min from first access to umbilical incision closure will be excluded from the analysis. The surgeon will rate surgical conditions every 10 min during the procedure and again at the end, using a 5-point scale (1=excellent, 2=good, 3=acceptable, 4=poor, and 5=inadequate).

In the economic analysis, direct costs will be based on operating and patient recovery times in the context of each hospital center, including time in the operating room and PACU and costs for the professionals monitoring the patient before extubation and resumption of spontaneous respiration. Indirect costs will be captured with the EuroQOL-5 dimensions quality of life questionnaire, lost productivity, and absence from work.

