## Introduction

Postoperative pain, especially shoulder pain, is commonly reported after laparoscopic gynecologic procedures [1]. Some studies have suggested that using a lower insufflation pressure may reduce the risk of postoperative pain [2]; however, there is no agreement on the optimal pneumoperitoneum pressure during gynecologic laparoscopic surgery or whether lower pressure would lead to clinically significant improvements without increasing operative complications. In a study of 100 laparoscopic cholecystectomy procedures randomly allocated to low-pressure pneumoperitoneum (8 mm Hg) or normal pressure (14 mm Hg), low pressure significantly decreased the frequency and intensity of postoperative shoulder pain, analgesics consumption, and length of hospital stay [2].

In gynecologic procedures, a study of 150 patients undergoing gynecologic laparoscopy randomly allocated to abdominal insufflation pressures of 8 mm Hg (n=54), 12 mm Hg (n=45), or 15 mm Hg (n=51), the pain scores were found to be significantly better with low insufflation pressure; however, there was a trend toward longer operation times and increased hemorrhage in this group [3]. A recent systematic review did not confirm this reported increase in operating time or blood loss with lower pressure; however, it did raise questions regarding whether the benefit of the observed reduction in postoperative pain could offset the decrease in the quality of surgical conditions [4]. The authors reported an association between lower pressure and increased risk of poorer surgical field visibility (relative risk 10.31; 95% CI 1.29-82.38).

Thus, there appears to be a consensus that low insufflation pressures can reduce postoperative pain [5-9], and this would appear to suggest a way to improve surgical conditions at lower insufflation pressures. For this purpose, it has been suggested that neuromuscular blockade (NMB) may help to maintain a sufficient intra-abdominal workspace at lower insufflation pressure [10]. NMB induces dose-dependent muscle relaxation that allows the muscles to stretch to their maximum length [11]. This may improve the surgical working space during laparoscopic procedures.

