### Eligibility Criteria for Participants

Eligible women scheduled for an elective laparoscopic or robotic gynecologic procedure with an expected duration <90 min performed under general anesthesia and requiring tracheal intubation (eg, cystectomy, hysterectomy, salpingo-oophorectomy) will need to satisfy the following criteria:

Age 18-60 yearsBody mass index between 20 and 30 kg/m^2^American Society of Anesthesiologists class 1 or 2Able to provide informed consent to trial procedures (eg, no speech or hearing impairment or language barriers)

Patients meeting any of the following criteria will be excluded:

PregnancySurgery for endometriosis, diagnostic laparoscopy with chromosalpingoscopy, myomectomy, or tube ligationAnticipated airway difficultyRequirement for rapid sequence inductionAnticipated intensive care unit admission or when extubation is not plannedHepatic or renal failureBaseline heart rate <50 bpmDocumented or suspected neuromuscular disorders, Guillain-Barré syndrome, cerebrovascular accidents with residual neurologic deficits, Parkinson disease, and myasthenia gravisPatients receiving fusidic acid or toremifene 24 hours before surgery and hormonal contraceptivesPatients receiving drugs for or affected by medical conditions that may prolong or shorten the duration of rocuronium effect (eg, aminoglycosides, magnesium)Patients with a history of allergy to rocuronium, neostigmine, or sugammadexAny condition making the administration of patient satisfaction questionnaire difficult or impossible.

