#### Allocation Concealment Mechanism

The study statistician will prepare the appropriate number of numbered, opaque, sealed envelopes for each center. These will be maintained at each center by an appropriately trained research nurse. At the time of anesthesia induction, the surgical nurse will open the relevant envelope, and the anesthesiologist will proceed to the allocated treatment.

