#### Methods for Any Additional Analyses

The main analysis will be on the whole study population. Additional analyses will be stratified by type of intervention. Also, analyses will consider uterus volume as a proxy for complexity of surgery.

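### Excluding operations that ran over 90 minutes selects on a post-randomisation variable: it truncates the duration and theatre-time cost comparisons and can bias pain and surgeon satisfaction if exclusions differ by arm

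*Protocol article*

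**What the plan says.** The exclusion stands in the protocol article under Secondary Outcomes: "Procedures lasting >90 min from first access to umbilical incision closure will be excluded from the analysis". It names no outcome and makes no exception. The Sample Size Calculation section shows that it is not confined to secondary outcomes. That section opens with "A sample size determination was conducted for the main outcome variable" and, citing a pilot at one centre, continues "we expect to lose no more than 5% of patients because of surgery durations >90 min", which is the reason given for enrolling 300.

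Two other sections fix the timing. Eligibility Criteria already restricts entry, before randomisation, to an "elective laparoscopic or robotic gynecologic procedure with an expected duration <90 min". Allocation Concealment Mechanism says "At the time of anesthesia induction, the surgical nurse will open the relevant envelope, and the anesthesiologist will proceed to the allocated treatment", so the actual duration is always observed after allocation.

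Duration from first access to umbilical closure, the same interval that defines the exclusion, is listed as a secondary outcome in Study Objectives and in Table 2. The Secondary Outcomes text bases direct costs on operating and recovery times. Methods for Any Additional Analyses says "The main analysis will be on the whole study population" without defining that population.

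**The concern.** Selecting patients on something that happens after randomisation is safe only if allocation cannot influence it. Here that is an open question which the trial itself sets out to examine. The Introduction cites a three-arm pressure trial in which, at 8 mm Hg, "there was a trend toward longer operation times and increased hemorrhage in this group". It also cites a systematic review that did not confirm longer operations, and a randomised trial of the same comparison (deep block at 8 mm Hg v moderate block at 12 mm Hg) that found no difference in duration. An analysis set should not depend on which of these proves right.

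The outcomes are exposed to different degrees:

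- **Duration, and costs built on theatre time.** Any value above 90 min is removed, so the upper tail is cut in both arms. If the arms truly differ, the difference is understated.
- **Pain AUC and surgeon satisfaction.** These are biased only if exclusions differ by arm and the excluded patients differ in outcome, as they could if difficult conditions prolong surgery.

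**Working it through.** **1. The plan's own figures.** Inputs from Sample Size Calculation: mean AUC 144 v 120, so a difference of 24; SD 60; two-sided 5%; 140 per group; stated power 92%. The standardised difference is 24/60 = 0.40. A two-sample t test with 140 per group has power 91.5%, which agrees with the plan. Allowing for a 5% loss, 280/0.95 = 294.7, or 295, against 300 enrolled. The sizing is sound, so the issue is which patients are analysed, not power.

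**2. Effect on the duration outcome.** The article gives no distribution of durations. Assume they are normal with SD 17 min in both arms and that group A takes longer. If a proportion p of an arm exceeds 90 min, let z be the standard normal point with upper tail p. Then

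- arm mean = 90 − 17z
- mean after exclusion = arm mean − 17λ, where λ = φ(z)/(1 − p)

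*Within the planned loss: 7% in A, 3% in B (average 5%).*

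- z = 1.476 (A) and 1.881 (B); true difference = 17 × (1.881 − 1.476) = 6.9 min
- λ = 0.1343/0.93 = 0.144 (A) and 0.0680/0.97 = 0.070 (B)
- observed difference = 6.9 − 17 × (0.144 − 0.070) = 5.6 min, about 18% too small

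*Above the planned loss: control mean 62, group A mean 72.*

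- 5.0% of B and 14.5% of A are excluded (average 9.8%)
- λ = 0.266 (A) and 0.108 (B)
- observed difference = 10 − 17 × (0.266 − 0.108) = 7.3 min, about 27% too small

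**3. Effect on the primary AUC.** If excluded patients score D units higher than retained patients in the same arm, dropping a proportion p lowers that arm's mean by pD. With the same D in both arms, the shift in A minus B is −(pA − pB) × D. A negative shift favours group A, since lower AUC means less pain. D is assumed to lie between 24 (the planned effect) and 60 (one SD).

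| Excluded, A v B | Average loss | Shift, D = 24 | Shift, D = 60 |
|---|---|---|---|
| 5% v 5% | 5% | 0 | 0 |
| 7% v 3% | 5% | −1.0 | −2.4 |
| 8% v 2% | 5% | −1.4 | −3.6 |
| 15% v 5% | 10% | −2.4 | −6.0 |

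At 7% v 3%, 2.4/24 = 10% of the planned difference. If the imbalance ran the other way, the sign would reverse.

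**4. Power with everyone analysed.** By t test for a difference of 24: 150 per arm at SD 60 gives 93.2%; 150 per arm at SD 62, in case long operations add variability, gives 91.6%. With the planned 5% exclusion (142.5 per arm, SD 60) it is 92.0%.

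**The case against.** **Allocation may not lengthen surgery.** Of the three sources cited on duration, two found no increase, and one of those is a trial of the same comparison. The reported trend comes from a trial described in terms of pressure alone, without deep block. The Insufflation Pressure section also lets pressure be adjusted to maintain the surgical field, which could limit any prolongation. This stands. A reader might infer that the rule favours the intervention and hides a harm of low pressure, but the documents do not establish that. They show only that it could, and if allocation affects neither duration nor who is excluded, the pain shift is zero.

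**The expected loss is small.** At no more than 5% overall, the shift in the primary AUC is modest beside 24 units. This also stands, with the caveat that the 5% comes from one centre's pilot, is not split by arm, and is carried over to a multicentre trial.

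**Is there a contradiction between sections?** A reader might set "The main analysis will be on the whole study population" against the exclusion and call them contradictory. The sentence that follows it introduces analyses by type of intervention, so the natural contrast is whole sample v subgroups. The wording does not say whether patients over 90 min belong to that population. It is unclear rather than contradictory.

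None of this rescues the rule for the duration outcome, whose upper tail is removed by definition whenever an operation exceeds 90 min.

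**Conclusion.** The concern holds. As written, the plan drops randomised patients according to a variable observed after allocation that is itself a secondary outcome, and the sample size section carries the rule into the primary analysis.

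The firmest damage is to duration and theatre-time costs: under normal durations with SD 17, a difference of about 6.9 min is reported as about 5.6 min within the planned loss, and 10 min as 7.3 min above it. For the primary AUC the plausible shift runs from zero to about 2.4 units at 7% v 3%. It is larger only if losses are more unequal or exceed the planned 5%. The duration distribution, the split by arm and the pain scores of excluded patients are assumptions; the article gives none of them.

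It would go too far to conclude that the pain result would be materially wrong. The case for change is that the rule gives up the protection of randomisation when removing it requires only wording.

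**What to change.** - Replace the exclusion sentence under Secondary Outcomes with a statement that primary and secondary outcomes are analysed in all randomised patients, in their allocated group, whatever the surgery duration.
- Keep 90 min only as the expected-duration criterion at eligibility.
- Report the number of operations over 90 min by arm.
- Retain the restriction to operations of 90 min or less only as a labelled sensitivity analysis.
- In Methods for Any Additional Analyses, state that the whole study population means all randomised patients.
- In Sample Size Calculation, remove the loss for surgery over 90 min. If an allowance for missing pain data is wanted, state it as a separate assumption; the pilot figure concerns long operations and cannot be relabelled for that purpose.

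The cost is wording, plus possibly a slightly larger SD from long operations. With all 150 per arm analysed, power stays at 91.6% even at SD 62, so the planned 300 suffices. The change should be made before outcome data are seen; the article defers the detailed analysis plan until 40 patients are enrolled.
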